#### Movement control exercise group

The patients in the movement control group will receive exercise treatment aimed at improving movement control of the lumbar spine as described in previous publications [21,34,69]. Patient education addresses awareness of positive and negative postural and movement related behaviour and increasing self-efficacy. Exercises are selected based on the direction of the impairment i.e. flexion, extension or frontal plane. The first step for patients is to learn to control the position and movement of the lumbar spine in different postures such as standing, squatting, 4 point kneeling and sitting. Movement control is practiced in combination with upper and lower extremity movements. In a second step, the difficulty level of exercise is increased through additional loading using long leavers or weights. If necessary, stretching/lengthening is applied after movement control has improved. Sports and strength training are allowed once good movement control is achieved.

#### General exercise group

Patients in this group are to be treated with the aim of improving endurance, strength and flexibility of the lumbar region. Patient education will address the importance of exercise and strength to reduce LBP. Exercises will address abdominals, erector spinae, gluteal, quadriceps and hamstrings muscle groups. The standardised exercise program starts in non-weight bearing positions and can be progressed by increasing load. Weights and resistance will be individually and progressively increased according to the guidelines of the American College of Sports Medicine [70]. The use of equipment is not standardised and will be left to the discretion of the therapists.

#### Main treatment contrast

The main difference between the two treatments is the instruction of movement control in the MCI group, which will not be applied in the general exercise group.

### Sample size calculation

Based on the results of our previous case series, inter-group difference in improvement of 0.9 points on the PSFS is to be used [71]. This difference is also clinically relevant as it displays an improvement of approximately 20% compared with an expected PSFS baseline score of 5 points. We used a standard deviation of 1.5 points, alpha was set at 0.05 and the power was set at 0.9. In each group, 48 patients are needed. Anticipating a 10% drop-out rate, the required sample size was set at 106 patients to be randomised.

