## Abstract

**Background:**

Non-specific low back pain (NSLBP) in subacute and chronic stages can be treated effectively with exercise therapy. Research guidelines recommend evaluating different treatments in defined subgroups of patients with NSLBP. A subgroup of patients with movement control impairment (MCI) improved significantly on patient specific function and disability in a previous case series after movement control exercises.

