## Background

Low Back Pain (LBP) is one of the major concerns of current health care [1-5]. Only 10% of LBP cases can be attributed to specific disorders like nerve root compression, vertebral fracture, tumour, infection, inflammatory diseases, spondylolisthesis or spinal stenosis. Consequently, NSLBP, in which the cause of symptoms is unknown, is diagnosed in about 90% of all patients and is a health problem of high economic importance [6].

Patients with NSLBP present diverse clinical findings, courses of disease and prognoses. They therefore make up a heterogeneous group of patients, which may explain why treatment effects in numerous studies looking at specific physiotherapy treatments in the NSLBP group are often discouraging. Identifying defined subgroups of patients within the NSLBP population has been a major focus in recent research [7-12]. Current European guidelines encourage outcome studies in subgroups of patients with a shared diagnostic pattern or prognosis that might benefit from specific treatments [1]. This research agenda is expected to reveal further evidence for the effect of treatments designed for specific subgroups [13]. Of 767 RCTs about the effect of conservative treatment on chronic LBP performed and published between 1982 and 2008, 68 publications examined manual or exercise therapy, of which five studies had an additional subclassification and matched treatments [14].

There is no evidence for the effectiveness of exercise in patients with acute LBP of a less than 6 week duration [1,15-17], but exercise therapy is effective in chronic and subacute LBP [16]. There is evidence that home exercise may be effective in decreasing pain and disability, but results have shown no significant difference between exercise types on work disability [1,18]. There is moderate evidence suggesting that exercise therapy may prevent recurrences of LBP, but there is no evidence for a difference in effect between types of exercise [19]. Individually designed exercise programs are recommended [17] but the question remains as to which types of exercise are effective for which subgroups of patients.

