Description: Specification of main symptoms and signs to classify the direction of movement control impairment

Two mechanisms are proposed to explain the impaired movement control behaviour. One relates to conditioning and habituation, which are important factors in motor learning. Patients use postures and movements that are potentially harmful due to maladaptive processes, like avoidance or overuse during the acute pain phase [28]. Another mechanism is non-awareness of the posture's pain provocation. Altered cortical representation of the lumbar spine in the presence of pain may play an important role [29]. Two point discrimination is decreased in patients with NSLBP, indicating changes in cortical representation because of NSLBP [30]. Both mechanisms can either be induced by pain or be the cause of pain.

It is hypothesised that, once movement control is impaired, it results in repetitive mechanical deformation of innervated tissue and leads to increased nociceptive input to the central nervous system and, therefore, pain [31]. All joint capsules, ligaments, tendons and muscles are possible pain sources, especially due to continuous strain or longstanding repetitive movements [31,32]. Repeated misuse of these tissues can also initiate the inflammatory cascade, a further cause of pain [33].

The inter-rater reliability of the clinical classification of NSLBP in MI and MCI is very high; in experts and raters with less experience, k = 0.85 and k = 0.6 respectively [34,35]. The inter- and intra-rater reliability of the previously described 6 active tests performed by the patient was evaluated as good to substantial [27]. Validity of MCI tests is supported by significantly different results in healthy subjects, with 0.75 positive MCI tests (95% CI 0.55-0.95) and low back pain patients with 2.21 positive MCI tests (95%CI 1.94-2.48, effect size d = 1.18) [36].

In a preceding prior controlled case series, 38 preselected patients with positive MCI tests were treated with an individualised movement control exercise program and showed improvements in MCI test performance associated with improvements in patient specific functional complaints and disability [37]. The present study will compare movement control training with general exercise in a randomised controlled trial.

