MCI exercises are often and falsely referred to as motor control exercises, spinal stabilisation or core stability exercises. While MCI exercises aim to improve function through repetitive normal use, the latter retrain delayed muscle activity first in order to improve control of the spine. Several trials and systematic reviews have evaluated the effect of stabilising exercises with conflicting results [38-42]. A recent randomised placebo-controlled trial with a specific stabilisation program in a population with chronic low back pain found a significant improvement in activity in both the short and long term when measured with a patient specific functional scale (PSFS), and a short term improvement for global impression of recovery and disability [43]. However, they did not subgroup the patients and the effects were not beyond the smallest minimal meaningful clinical change.

The general exercise treatment is based on treatments used in previous studies. Exercises were developed to improve endurance, strength and flexibility of the spinal tissues [44]. Experimental studies have shown that these exercises involve many global and local muscles and improve the stability of the spine [45,46]. In an RCT of patients with subacute and chronic NSLBP, a course of only general exercise was compared with a combination of general exercise and stabilisation exercise. Immediately after treatment, disability was significantly lower in the general exercise group. No differences were found in other outcomes or at follow-up time points [47].

Psychosocial factors have an important impact on treatment outcome in NSLBP patients who also show non-acute [48] depression, pain catastrophising, fear of pain and avoidance. These aspects are part of the fear-avoidance model of chronic pain, and previous data has reported its various effects on treatment outcome [49]. Pain-related fear and subsequent avoidance of movements that patients believe to be harmful can also lead to disability and physical deconditioning [50]. In our study patients with a high risk of psychosocial problems are excluded based on an assessment with the Örebrö Musculoskeletal Pain Questionnaire (ÖMPQ) [51,52]. This influential variable will be observed using the Fear-avoidance beliefs questionnaire.

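### The 0.9-point between-group difference is credited to a case series with no described general-exercise comparator, and the 90% power built on it holds only for a one-sided test

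*Protocol article*

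**What the plan says.** The Sample size calculation gives two grounds for its effect size. The first is empirical: "Based on the results of our previous case series, inter-group difference in improvement of 0.9 points on the PSFS is to be used". The second is clinical relevance: "it displays an improvement of approximately 20% compared with an expected PSFS baseline score of 5 points". With SD 1.5, alpha 0.05 and power 0.9, it arrives at 48 patients per group and, allowing for 10% drop-out, 106 randomised. It does not say whether alpha is one-sided or two-sided.

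The Background describes the earlier work: "38 preselected patients with positive MCI tests were treated with an individualised movement control exercise program". The abstract agrees that patients "improved significantly on patient specific function and disability in a previous case series after movement control exercises". The Background applies the word controlled to this series but describes no comparator group and reports no result for one.

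Hypothesis 1 is a comparison of movement control exercise with general exercise on the PSFS.

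**The concern.** The quantity that drives the sample size is a difference between two arms. A series in which every described patient had the experimental treatment contains no information on what general exercise achieves, so it cannot supply that difference. A reader of the sample size section would nevertheless take 0.9 as something already observed, and the 90% as the chance of success under an observed effect.

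The comparator here is active: the Background says that exercise therapy works in subacute and chronic low back pain. The difference between the arms is therefore the input most in need of support, and the power is very sensitive to it. If the trial ends without significance, readers will judge how informative that is by the power the protocol claimed.

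**Working it through.** **1. Source of the difference.** Three places were set side by side.
- Sample size calculation: an inter-group difference, taken from the authors' own previous case series (reference 71).
- Background: 38 patients, all on movement control exercise, no comparator described (reference 37).
- Abstract: improvement after movement control exercise.

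The reference list is not shown, so it is an inference that 71 and 37 are the same work. It rests on the shared description as an own case series and on the article describing no other. Nowhere does the article report a PSFS result under general exercise, or the size of the PSFS change in the series.

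**2. The plan's own figure.** Inputs from the Sample size calculation: difference 0.9, SD 1.5 (standardised difference 0.9/1.5 = 0.6), alpha 0.05, power 0.9. The normal-approximation formula is n per arm = 2 × (z_alpha + z_beta)² / 0.6².
- One-sided: 2 × (1.645 + 1.282)² / 0.36 = 47.6, so 48. This matches.
- Two-sided: 2 × (1.960 + 1.282)² / 0.36 = 58.4, so 59. This does not match. With the t distribution the result is 59.4, so 60.

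The total of 106 equals 96 × 1.10 = 105.6 rounded up. Dividing instead, 96/0.9 = 106.7, gives 107, a trivial difference.

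**3. Power of the fixed sample.** With 48 analysed per arm, the standard error of the difference is 1.5 × √(2/48) = 0.306. The noncentrality is the difference divided by 0.306, on 94 degrees of freedom. The differences below 0.9 are assumptions, because the article gives no estimate between the arms.

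| True difference | Noncentrality | Power, two-sided 0.05 | Power, one-sided 0.05 |
|---|---|---|---|
| 0.9 | 2.94 | 83% | 90% |
| 0.7 | 2.29 | 62% | 73% |
| 0.5 | 1.63 | 37% | 49% |

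The step from 90% to 83% in the first row comes from sidedness alone. Only the fall down each column reflects uncertainty about the difference.

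These are t-test figures. Data analysis plans a Mann-Whitney U test, for which they are an approximation.

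**4. What a non-significant result could mean.** On the same assumptions, the 95% CI has half-width 1.986 × 0.306 = 0.61. An observed difference between 0.9 − 0.61 = 0.29 and 0.61 would be non-significant at the two-sided 5% level and still have a CI that includes 0.9.

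**The case against.** The strongest reply is that 0.9 does not need the case series. The section already calls the difference clinically relevant, and 0.9/5 = 18% fits its approximate 20%. Power is always conditional on a chosen difference, and a target of this kind is a legitimate basis. This stands: neither the value of 0.9 nor the arithmetic fails because of the attribution.

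The reference numbers differ and the Background uses the word controlled, so the cited source might hold more than the article reports. That stands as a caveat. But the plan itself calls its source a case series, and no contrast with general exercise is described anywhere.

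Some stronger readings are tempting and are not supported:
- **That 0.9 is really the gain within the movement control patients, so the true contrast must be smaller.** No passage gives the PSFS change in the series. If it was larger than 0.9, the figure may already allow for improvement under general exercise.
- **That scaling 0.9 to the baseline score shows between-group and within-patient change being confused.** The wording is loose, but expressing a between-group difference as a share of baseline is a permissible scaling.
- **That the Background predicts no difference, because "there is no evidence for a difference in effect between types of exercise".** That sentence is about preventing recurrences, and a companion statement is about work disability. Neither concerns the PSFS or patients with movement control impairment, and the trial's rationale is that such a subgroup may respond differently.
- **That the plan defines success as p < 0.05 alone.** Data analysis sets a significance level and does not exclude a reading against clinical relevance. Such a reading is commonly left to an analysis plan, which is not shown.

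**Conclusion.** The point holds in limited form. The article attributes a between-group difference to a series which, as described, cannot provide one, so the empirical support for the main design input is missing. The relevance argument remains and can carry 0.9 as a target. How far 0.9 might be from the true difference cannot be derived from the article.

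The consequence that can be computed concerns the stated power. With 48 analysed per arm and SD 1.5, 90% at 0.9 requires a one-sided 5% test; two-sided it is about 83%, and 59 to 60 per arm would be needed for 90%. This sidedness shortfall is separate from the source of 0.9, but both belong in one corrected statement. At assumed differences of 0.7 and 0.5, power drops to about 62% and 37% two-sided, or 73% and 49% one-sided, so the sensitivity to the unsupported input is substantial under either convention. All of this assumes SD 1.5, 10% drop-out as planned, and the t test as a stand-in for Mann-Whitney.

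**What to change.** In Sample size calculation:
- Remove the statement that the inter-group difference comes from the case series.
- State 0.9 as the target clinically relevant between-group difference.
- Name the sidedness and restate the power of the fixed sample: about 83% two-sided at 0.9 (90% only one-sided), with 62% at 0.7 and 37% at 0.5 two-sided (73% and 49% one-sided), marked as a t-test approximation and with the smaller differences marked as assumptions.

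As a secondary suggestion, in Data analysis or the analysis plan: report the between-group PSFS difference with its 95% CI and read it against 0.9, so that a non-significant result whose CI includes 0.9 is not taken as no difference. The Background already applies a similar standard to an earlier stabilisation trial, noting that "the effects were not beyond the smallest minimal meaningful clinical change".

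The cost is a few sentences, with no extra patients or data. The downside is that the stated power becomes less favourable.

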### Hypotheses

1. In NSLBP patients with MCI, treatment with movement control exercises will result in a significant decrease in disability compared to general exercise, measured with the patient specific functional scale.

2. In NSLBP patients with MCI, improvement in motor control of the lumbar spine, assessed with standardised clinical tests, is associated with functional improvement and pain reduction.

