### Data analysis

The comparability of both groups on prognostic and outcome variables at baseline will be analysed using two-sample t-tests in data with a normal distribution, Wilcoxon tests in non-parametric data and Chi-square tests in nominal data. An intention-to-treat analysis will be utilised in which all participants will be analysed in the group to which they were originally assigned. Differences between the groups over time are measured by Mann-Whitney-U-test. The influence of baseline differences on outcome measurements will be assessed in a multivariable linear regression analysis. A regression analysis of the factors being positive or negative predictors will be conducted based on covariates measured at baseline. Statistical significance is set at p < 0.05.

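### 48 patients per group does not give 90% power at two-sided 5% on the stated inputs: power is about 83%, unless an undeclared one-sided test is intended

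*Protocol article*

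**What the plan says.** All the inputs stand in one paragraph of the protocol article, under Sample size calculation:

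- Effect: "inter-group difference in improvement of 0.9 points on the PSFS is to be used".
- Variability: "We used a standard deviation of 1.5 points".
- Error rates and result: "alpha was set at 0.05 and the power was set at 0.9. In each group, 48 patients are needed".
- Total: "Anticipating a 10% drop-out rate, the required sample size was set at 106 patients to be randomised".

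The same paragraph justifies the 0.9 points as roughly a fifth of an expected baseline score of 5.

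Three other statements bear on whether the test is one- or two-sided:

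- Data analysis, on the threshold: "Statistical significance is set at p < 0.05".
- Data analysis, on the between-group test: "Differences between the groups over time are measured by Mann-Whitney-U-test".
- Hypotheses, item 1: "treatment with movement control exercises will result in a significant decrease in disability compared to general exercise".

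None of them says one-sided or two-sided.

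**The concern.** The article prints a complete set of inputs and a result, so the result can be checked without any further document. At the level most readers will assume for p < 0.05, namely two-sided, the result does not follow from the inputs.

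This is the only power justification given for the primary outcome. If the test is two-sided, a null finding on the PSFS would be read as coming from a trial with a 10% risk of missing the target difference, when the risk is nearly twice that. If the test is one-sided at 5%, the false-positive rate in favour of movement control exercise is 5%, against 2.5% in that direction for a two-sided 5% test, and the reader has not been told. The comparator is an active treatment that the article itself describes as well established, so a result in favour of general exercise is possible and would matter.

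**Working it through.** **Inputs** (Sample size calculation): difference δ = 0.9; SD σ = 1.5; alpha = 0.05; power = 0.90; two equal groups. Standardised difference: 0.9/1.5 = 0.60.

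**Formula** (comparison of two means, normal approximation), per group:

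n = 2 (z_alpha + z_power)² (σ/δ)², with (1.5/0.9)² = 2.778 and z_power = 1.2816.

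**Step 1. Reproduce the printed figure.** One-sided 5%, z_alpha = 1.6449:

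n = 2 × (1.6449 + 1.2816)² × 2.778 = 2 × 8.564 × 2.778 = 47.6, so 48.

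This matches the article.

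**Step 2. The same inputs, two-sided 5%**, z_alpha = 1.9600:

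n = 2 × (1.9600 + 1.2816)² × 2.778 = 2 × 10.507 × 2.778 = 58.4, so 59.

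The exact t-test calculation (noncentral t) gives 59.4, so 60.

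**Step 3. Power actually available, two-sided 5%.** With 48 per group the noncentrality is 0.60 × √(48/2) = 2.939. By the normal approximation, power = Φ(2.939 − 1.960) = Φ(0.979) = 83.6%. The Mann-Whitney column uses an efficiency of 3/π = 0.955 relative to the t test, which holds for normal data.

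| Evaluable per group | t test | Mann-Whitney, if data are normal |
|---|---|---|
| 48 (as stated) | 82.9% | 81.1% |
| 47.7 (106 randomised, 10% lost) | 82.6% | 80.9% |
| 53 (106 randomised, none lost) | 86.4% | 84.8% |

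The type II error with 48 per group is therefore 17.1% (t test) or 18.9% (Mann-Whitney), not 10%. Even with no drop-out the two-sided power stays below 90%.

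**Step 4. What 48 per group does deliver at 90%, two-sided.**

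- Detectable difference at SD 1.5: 1.5 × (1.9600 + 1.2816)/√24 = 0.99 by the normal formula, and 1.00 by t test.
- SD at which 0.9 points is detectable: 0.9 × √24/(1.9600 + 1.2816) = 1.36 by the normal formula, and 1.35 by t test. With 47.7 per group the t-test figure is 1.34. Going from 1.5 to 1.34 means that baseline adjustment must remove 1 − 1.34²/1.5² = 20% of the variance.

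**Step 5. Another route to 48.** A difference of exactly 20% of a baseline of 5 is 1.0 point. Two-sided: 2 × 10.507 × (1.5/1.0)² = 47.3, so 48. This also reproduces the number, but with a difference that the article does not state.

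**The case against.** The strongest reply is that the arithmetic is correct if the test is one-sided, and that Hypothesis 1 points that way by predicting a benefit of movement control exercise. The arithmetic part stands. The inference does not: a directional hypothesis is routinely tested two-sided, and neither Hypotheses nor Data analysis declares a one-sided test. On this reading the defect changes form, to an undeclared one-sided 5% criterion, but does not go away.

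A reader might infer from Step 1 that the authors did use a one-sided alpha. The documents do not settle this. A two-sided calculation with 1.0 point gives 48 as well, and the remark about a fifth of the baseline score makes that route plausible. It does not rescue the printed text, since the stated difference is 0.9, but how 48 arose is unknown. Nor does anything in the article show an intention to judge success one-sided.

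It can also be said that the loss attributed to Mann-Whitney is not established. This stands in part: the 81% assumes normal data, and the article gives no distribution for the PSFS. For other shapes the test can be as efficient as the t test or more so. The 81% therefore needs its condition attached, and the main point does not depend on it.

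A reader might further infer that the drop-out step is wrong, because 96 × 1.1 = 105.6 gives 106 whereas 96/0.9 = 106.7 gives 107. That is a rounding difference. It moves two-sided t-test power from 82.9% to 82.6% and is no part of this point.

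Finally, 83% exceeds the 80% that many trials accept, and neither the design nor the analysis is invalidated. That is true, and it is why the remedy is a corrected statement and not a larger trial.

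**Conclusion.** The sample size statement is wrong as written. With a difference of 0.9, an SD of 1.5, alpha 0.05 and power 0.9, a two-sided test needs 59 to 60 per group, not 48. One of two things holds:

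- the test is two-sided, and power for 0.9 points is about 83% by t test (about 81% for Mann-Whitney under normality), or
- the test is one-sided at 5%, the 90% is about right on the normal formula, and the protocol fails to say so.

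The flat statement that the trial is underpowered goes further than the document allows, because the shortfall is conditional on a two-sided test. What is certain is that the printed 90% cannot stand beside an undeclared, conventionally two-sided p < 0.05. The figures rest on the article's own difference and SD, equal groups, and 48 evaluable patients per group; with 10% lost from 106 (95.4 completers) they fall by about 0.2 to 0.3 percentage points.

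**What to change.** Keep 106 randomised. In Data analysis, state that the primary test is two-sided at 5%. In Sample size calculation, replace the power claim along these lines: 106 patients randomised, leaving about 95 completers, give about 83% power (t test) to detect 0.9 PSFS points with SD 1.5 at two-sided alpha 0.05, and about 81% with the Mann-Whitney test if the data are normally distributed; equivalently, 90% power (t test) for about 1.0 point.

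If the primary analysis is adjusted for baseline PSFS, power may be stated on that basis instead. It reaches 90% for 0.9 points if the residual SD is about 1.34 or less, and the source of that SD should be given.

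The cost is one reworded paragraph, one added phrase and a less favourable power figure. No patients are added, and the correction can be made before results are known: the article puts the end of inclusion at the end of 2011 and results in 2013. Holding 90% by numbers alone would instead take 60 completers per group, or 120/0.9 = 133.3, so 134 randomised; that is not asked for here.
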